## Outcome measures

The primary outcome is the presence or absence of a clinical signature of imminent eclampsia, unique both from women with preeclampsia and healthy normotensive pregnant women. To determine this, we have designed a standardised questionnaire collecting the following information:

| Maternal characteristics | Obstetric/booking information | Signs/symptoms | Eclampsia | Outcome |
| --- | --- | --- | --- | --- |
| First name | Gestation at booking | Highest systolic BP | Date of onset | Delivery date |
| Last name | Date at booking | Highest diastolic BP | Location of onset | Gestation at delivery |
| Maternal age | Estimated due date | Highest proteinuria | Prior magnesium sulphate | Indication for delivery |
| Address | How was due date estimated | Lowest platelet count |  | Mode of delivery |
| Race | Height | Highest AST |  | Live born |
| Marital status | Weight | Lowest haemoglobin |  | Sex |
|  | Antenatal care | Edema |  | Birthweight |
|  | Gravidity/parity | Tendon reflexes |  | Apgar at 5 minutes |
|  | Previous viable pregnancy outcome | Headaches, severity and onset |  | Neonatal outcome |
|  | Systolic BP at booking | Visual disturbances/type and onset |  | Number of days in hospital (maternal) |
|  | Diastolic BP at booking | Epigastric pain |  | Adverse maternal outcome |
|  | Proteinuria at booking | Tightness in chest |  |  |
|  | Antihypertensive medication | Shortness of breath |  |  |
|  | Tobacco/alcohol/drug use | Focal neurological deficit |  |  |
|  | Diabetes | Nausea/vomiting |  |  |
|  | Chronic hypertension | Confusion |  |  |
|  | Cardiovascular disease | Twitching/jerking of extremities |  |  |
|  | Anaemia | Mind state |  |  |
|  | HIV status | Concentration |  |  |
|  | Respiratory disease | Speech |  |  |
|  | Inflammatory bowel disease | Hearing |  |  |
|  | Autoimmune disease | Changes in moods |  |  |
|  | Malaria | Dizziness |  |  |
|  | Renal disease | Weakness or paralysis |  |  |
|  | Neurological disease | Jitters/nervousness |  |  |
|  | Medication use |  |  |  |

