## Statistical analysis

Data will be collected and analysed in clinically relevant categories with I2 or Mann-Whitney U tests used to detect difference between groups. We will compare data from women with eclampsia to those with i) preeclampsia and ii) normotensive pregnancies, to determine the unique signs and symptoms that precede eclampsia. Odds ratios will be used to determine strength of association for clinical characteristics significantly associated with eclampsia. We will also attempt to create a predictive score for eclampsia.

1. Knight M. Eclampsia in the United Kingdom 2005. *BJOG: An International Journal of Obstetrics & Gynaecology.* 2007;114(9):1072-1078.

3. Frias AE, Jr., Belfort MA. Post Magpie: how should we be managing severe preeclampsia? *Current opinion in obstetrics & gynecology.* 2003;15(6):489-495.

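### Choosing the signature by separate significance tests on 25 signs invites false features and does not measure whether eclampsia can be told apart

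*Protocol*

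**What the plan says.** Under Outcome measures the protocol states: "The primary outcome is the presence or absence of a clinical signature of imminent eclampsia". The same sentence requires this signature to set eclampsia apart from each of the two comparison groups, preeclampsia and normotensive pregnancy. The Study design section adds that the signature should serve to predict impending eclampsia. The questionnaire table under Outcome measures has a Signs/symptoms column that runs from highest systolic BP to "Jitters/nervousness".

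The route to the outcome is in Statistical analysis:

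- Methods: "Data will be collected and analysed in clinically relevant categories", using chi-squared (the symbol is garbled in the text at hand) as one test and "Mann-Whitney U tests used to detect difference between groups" as the other.
- Comparisons: "We will compare data from women with eclampsia to those with i) preeclampsia and ii) normotensive pregnancies", the purpose being "to determine the unique signs and symptoms that precede eclampsia" in the protocol's words.
- Filter: "Odds ratios will be used to determine strength of association for clinical characteristics significantly associated with eclampsia".

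A predictive score is mentioned last, as something the study will also try to produce. The section names no significance level, multiplicity adjustment, joint model or measure of discrimination.

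**The concern.** The item-by-item tests are not presented as description alone. The section says that the group comparisons determine which signs are unique to eclampsia, and significance decides which characteristics receive an odds ratio. That makes per-item significance the stated route to the primary outcome. Two difficulties follow.

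First, many signs are screened and no allowance for that is named, so some may pass by chance. Many of the signs can be expected to differ from healthy normotensive women in any case, because hypertension and organ involvement define preeclampsia in the Inclusion criteria. For those signs, only the test against preeclampsia acts as a filter.

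Second, a significance test asks whether group frequencies differ. A predictive signature has to show how well women who will have a seizure can be told from those who will not. A sign can pass the first test and be nearly useless for the second. A sign that helps only in combination with others can fail the first and be dropped.

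At stake is a declared signature that does not separate eclampsia from preeclampsia. The Background section intends the resulting tool to direct preventive treatment to the right women.

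**Working it through.** **Inputs**

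- Candidate signs: m = 25, counted in the Signs/symptoms column of the Outcome measures table.
- Comparisons per sign: 2 (against preeclampsia and against normotensive women), from Statistical analysis.
- Significance level: not stated. Assumed two-sided 0.05, with 0.01 and 0.10 shown as a range.
- Sample size: not stated. The counts in step 5 are assumed, for illustration only.

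The protocol gives no error rate or power figure, so there is none to reproduce.

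**Step 1. Independent signs, none truly different from preeclampsia, all truly different from normotensive women.** Only the preeclampsia test filters.

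- Expected false features: 25 × 0.05 = 1.25.
- Chance of at least one: 1 − 0.95^25 = 0.723.
- Range by level: 1 − 0.99^25 = 0.222 at 0.01; 1 − 0.90^25 = 0.928 at 0.10.

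**Step 2. Correlated signs.** The list overlaps: systolic with diastolic BP, and confusion with mind state, concentration and speech. With equally correlated normal test statistics, the chance of at least one false feature at 0.05 is:

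| Correlation between signs | Chance |
| --- | --- |
| 0.2 | 66% |
| 0.3 | 61% |
| 0.5 | 47% |

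**Step 3. Same direction required against both groups.** If a sign truly differs from normotensive women, only one tail of the preeclampsia test can produce a false feature, so the error per sign is 2.5%.

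- Independent signs: 1 − 0.975^25 = 0.469.
- Correlations 0.2, 0.3 and 0.5: 36%, 32% and 23%.

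**Step 4. Signs null in both comparisons, same direction required.** The two test statistics share the eclampsia group. With a correlation of 0.5 between them (equal group sizes), the chance that both are significant in the same direction is 0.0092 per sign.

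- Expected false features: 25 × 0.0092 = 0.23.
- Chance of at least one, independent signs: 1 − (1 − 0.0092)^25 = 0.207.
- If the correlation between the two comparisons is 0.25 or 0.75: 9% or 38%.

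**Step 5. Significance against discrimination.** Take a sign present in 65 of 100 women with eclampsia and 200 of 400 comparators.

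- Chi-squared = 500 × (65×200 − 35×200)² / (100 × 400 × 265 × 235) = 7.23, so p = 0.007 (0.010 with continuity correction).
- Odds ratio = (65×200)/(35×200) = 1.86.
- Sensitivity 0.65, specificity 0.50, positive likelihood ratio 0.65/0.50 = 1.3.
- AUC of the single binary sign = (0.65 + 0.50)/2 = 0.575, where 0.50 is chance.

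A second example gives the same picture. A sign present in 30% of comparators, with an odds ratio of 2, has sensitivity 46%, specificity 70% and AUC 0.58, yet reaches 80% power at 141 women per group.

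**Step 6. Would multiplicity control alone be enough?** Bonferroni over 25 signs (0.05/25 = 0.002) brings the chance in step 1 to 1 − 0.998^25 = 0.049. It leaves step 5 unanswered, because it still measures association.

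**The case against.** The best defence is that multiplicity control, discrimination measures and validation are commonly left to an SAP, which may exist, and that the absence of adjustment is inferred from silence. That stands for the omissions taken singly. It does not remove the point, because the protocol itself fixes the filter: item-by-item tests determine the unique signs, and odds ratios follow only for those that pass.

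A second defence is that odds ratios are offered as strength of association and that the score is listed separately. That is a fair reading of the sentence. But the primary outcome is still a yes-or-no signature, and no other route to it is stated.

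Several stronger readings are tempting but unsupported:

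- A reader might infer that a spurious signature is more likely than not. That needs independent or only weakly correlated signs and the most lenient reading of uniqueness. The Outcome measures section asks for uniqueness from both groups, and under the other scenarios the chance falls below one half.
- A reader might add the booking items to the count. The section looks for signs and symptoms, and the booking column includes dates that are not candidate features.
- A reader might put a figure on the inflation of the score's accuracy. The protocol gives no sample size and does not say that the score is a refit of screened items.
- A reader might put a figure on information lost to categories. The protocol does not say two categories, and it names a rank test.

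**Conclusion.** The concern holds as a weakness in a stated rule. Followed as written, the protocol can declare unique features at an error rate well above 5%, and it does not measure the discrimination that its primary outcome implies.

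At an assumed two-sided 5%, and with no true separation from preeclampsia, the chance of at least one false feature runs from 72% (independent signs) through 66% to 47% (correlated signs) and 47% to 23% (same direction against both groups) to about 21% (null in both). The 72% is the top of that range, not the expected result. All these figures depend on the assumed level; at 1% the independent-sign figure is 22%. The example with p = 0.007 and AUC 0.575 uses assumed counts and shows only that significance and discrimination can part company. It does not predict this study's results.

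**What to change.** Amend Statistical analysis as follows:

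1. Report odds ratios, sensitivity, specificity and likelihood ratios with confidence intervals for all 25 signs in both comparisons, whether significant or not, with false-discovery-rate control.
2. State that items for the predictive score will not be selected by univariable significance.
3. Base the conclusion on a signature on the optimism-corrected c-statistic, with 95% confidence interval, of a multivariable model, using a bootstrap that repeats every modelling step. Make preeclampsia the main comparison and report the normotensive comparison as well, since the primary outcome names both.
4. Fix the c-statistic threshold for declaring a signature before analysis. The protocol gives no basis for a particular value, so the investigators must choose and justify it.
5. Record BP and laboratory values raw, so that they can be analysed as continuous. If they are captured only in categories, no later plan can recover them.

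The choice of modelling technique can be left to the SAP. The cost is revised wording, modest programming and raw-value fields in the database, with no extra participants. The drawback is that the reported accuracy will probably look less favourable.
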